#### Outcome definitions and measures

Acute kidney injury will be defined as an increase in serum creatinine of ≥ 50% from baseline or need for renal replacement therapy within the first 7 postoperative days [22].

Acute myocardial injury will be defined as an increase in high-sensitivity troponin concentration within the first 7 postoperative days according to the definition of “myocardial injury and infarction associated with non-cardiac procedures” set forth in the Fourth Universal Definition of Myocardial Infarction (2018) [23].

Serum creatinine and high-sensitivity troponin I or T (whichever is used in each center) will be measured before surgery (baseline; within the last 30 preoperative days) and on postoperative days 1, 2, 3, and 7. When patients are discharged earlier, serum creatinine and high-sensitivity troponin will be measured on the day of discharge. Additional serum creatinine and high-sensitivity troponin concentrations will be recorded during the initial 30 postoperative days on an as-available basis.

Non-fatal cardiac arrest will be defined as successful resuscitation from ventricular fibrillation, sustained ventricular tachycardia, asystole, or pulseless electrical activity requiring cardiopulmonary resuscitation, pharmacological therapy, or cardiac defibrillation.

Infectious complications will be defined according to the “Standardised Endpoints in Perioperative Medicine (StEP)” initiative [24] and include fever, respiratory infection, neurological infection, urinary system infection, colitis or infection with *Clostridium difficile*, endometritis, surgical site infection, deep incisional surgical site infection, organ or space surgical site infection, unknown infection with pathogenic organisms in tissue or fluid, and sepsis.

Data for the outcome assessment will be collected using medical records and telephone interviews on postoperative days 3, 7, 30, and 90.

Serious adverse events will be documented during the trial and will be reported to the primary ethics committee.

### Statistical considerations and methods

#### Sample size

The sample size was estimated from the anticipated incidence of the composite primary outcome of at least one severe complication or death within 7 days after surgery. We expected an incidence of 25% in the routine management group (adapted from own data and literature [2, 25, 26]) and 17% in the personalized management group. The assumed absolute risk reduction of 8% is a conservative estimate based on a previous trial investigating the effect of individualized blood pressure management compared to routine blood pressure management on postoperative organ failure [13].

We will use a group sequential-design with one unblinded interim analysis using the O’Brien-Fleming spending function [27]. A total sample size of 1144, i.e., 572 patients per group will provide 90% power to detect a difference of 8% between the groups at a significance level of 0.05 using a two-sided test of proportions with continuity correction including an unblinded interim analysis after 50% of patients are recruited. Allowing a total drop-out rate of 10% (assuming an 8% drop-out rate before randomization and 2% after randomization), we plan to recruit 1272 patients. We assume that all patients will remain in their allocated treatment group throughout the observation period. PASS version 16.0.3 was used for the sample size calculation.

#### Statistical analyses

Descriptive analysis will be performed to describe the patient characteristics and clinical data. The primary and secondary outcomes will be analyzed according to the intention-to-treat principle. The primary outcome analyses (interim as well as final analysis) will be conducted using a two-sided test of proportions with continuity correction. When a total of 636 patients will have been observed for 7 days, an unblinded interim analysis will be performed. If the resulting *p*-value is < 0.0015 one-sided, the null hypothesis will be rejected, and the trial will be stopped for efficacy. Otherwise, recruitment will be continued. At the end of the trial, the statistical test for the primary outcome will be performed at a significance level of 0.049 two-sided.

In secondary outcome analyses, the incidence of each of the individual components of the primary outcome and of the additional secondary outcomes will be analyzed using a two-sided test of proportions with continuity correction. In additional analyses, the primary outcome and its individual components will be treated as time-to-event outcomes. Due to the competing event death, all time-to-event outcomes will be assessed using Aalen-Johansen estimators and accompanied by effect estimates based on cause-specific Cox regressions. In further analyses, the primary and secondary outcome analyses will be repeated in the per-protocol population. As a sensitivity analysis, the primary outcome will be analyzed using a mixed logistic regression model including a fixed effect for the random group and a random effect for the center to account for the cluster structure in the data. In further sensitivity analyses, regression models (logistic and cause-specific Cox regression) including potential prognostic baseline variables will be used.

If more than 5% of values are missing for the primary outcome, we will use multiple imputation in a sensitivity analysis. The number of imputations for multiple imputation will be chosen depending on the proportion of missing data according to White et al. [28].

A full statistical analysis plan will be developed before any data are evaluated.

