## Methods/design

### Trial design

The proposed trial will be conducted in accordance with the ethical principles based on the Declaration of Helsinki [18] and the ICH E6 R2 guidelines for good clinical practice. The trial was approved by the ethics committee Hamburg (Ethikkommission der Ärztekammer Hamburg, Hamburg, Germany, registration number 2022–100879-BO-ff) acting as the primary ethics committee for this trial. Secondary ethics committee approvals will be obtained for each trial site before patient recruitment starts. The trial was registered at ClinicalTrials.gov (NCT05416944) on June 14, 2022. This article adheres to the Standard Protocol Items: Recommendations for Interventional Trials (SPIRIT) statement (Additional file 1) [19].

IMPROVE-multi will be a multicenter randomized controlled blinded (participating patients, outcome adjudicators, and data analysts) clinical superiority trial in 1272 high-risk patients having elective major abdominal surgery. We plan to enroll patients at approximately 16 German university medical centers. The trial coordinating center will be the University Medical Center Hamburg-Eppendorf, Hamburg, Germany.

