**Fig. 1 Fig1:**
[figure not shown]
Flowchart illustrating patient screening, enrollment, randomization, trial intervention, and the primary outcome

**Table 1 Tab1:** Frequency and scope of trial visits

	Preoperative	Perioperative	Postoperative						
Day	− *x* to − 1	0	1	2	3	4–6	7	30	90
Visits/contacts	I	II	III	IV	V	VI	VII	VIII	IX
**Informed consent**	X								
**Baseline assessment (i.e., demographic data, medical history)**	X								
**Preoperative automated blood pressure monitoring**	X								
**Blood sampling #1 (baseline values)**	(X)	X							
**Randomization**		X							
**Perioperative blood pressure management**		X							
**Blood sampling #2, 3, 4, and 5**			X	X	X	(X)	X^a^		
**Primary outcome assessment**							X		
**Secondary outcome assessments**					X		X	X	X

^a^If the patient is discharged earlier than day 7, creatinine and high-sensitivity troponin concentrations will be required on the day of hospital discharge

Written informed consent will be obtained by dedicated trial personnel. Baseline demographic and medical characteristics will be recorded and entered in an electronic Case Report Form (eCRF). Preoperative automated blood pressure monitoring will be performed either at home or in the hospital for one night using upper arm cuff oscillometry at 30-min intervals. After excluding artifacts, we will calculate the mean of the nighttime mean arterial pressures. We will define nighttime as 00:00 to 06:00 h [20, 21].

Patients will be randomized in a 1:1 ratio using central block-wise randomization with variable block length stratified by centers with an electronic tool to personalized blood pressure management or to routine blood pressure management. The randomization will be performed directly before the induction of general anesthesia.

In patients assigned to personalized management, intraoperative mean arterial pressure will be maintained at least at the mean of the nighttime mean arterial pressures. If the mean of the nighttime mean arterial pressures will be lower than 65 mmHg, the intraoperative mean arterial pressure will be maintained at least at 65 mmHg; if the mean of the nighttime mean arterial pressures will be higher than 110 mmHg, the intraoperative mean arterial pressure will be maintained only at least at 110 mmHg. The intervention period will start at the induction of general anesthesia and will end 2 h after the end of surgery.

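### The primary test is not stratified by centre, although randomization is, and it carries a continuity correction: valid and adequately powered, but conservative, so a modest gain is available at no cost

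*Protocol article*

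**What the plan says.** The Protocol subsection of the methods fixes the allocation: "Patients will be randomized in a 1:1 ratio using central block-wise randomization with variable block length stratified by centers". Under Trial design the article gives the number of centres: "We plan to enroll patients at approximately 16 German university medical centers".

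Under Statistical analyses it fixes the confirmatory test for both looks: "The primary outcome analyses (interim as well as final analysis) will be conducted using a two-sided test of proportions with continuity correction". The interim boundary is a one-sided p-value below 0.0015, and the final level is 0.049 two-sided. Centre appears only afterwards: "As a sensitivity analysis, the primary outcome will be analyzed using a mixed logistic regression model", with a random centre effect. Regression models with prognostic baseline variables are listed as further sensitivity analyses. No reason is given for leaving centre out of the primary test.

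Under Sample size the same corrected test is used, with 25% against 17%, 1144 patients and 90% power. No between-centre variance is stated.

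**The concern.** Blocking within centre balances centre differences between the arms. An unstratified variance still counts those differences as noise. If event rates vary by centre, the standard error is then larger than the true sampling variation and the test rejects too rarely. Variation is plausible, because eligibility is broad and the troponin assay behind one component is a local choice ("high-sensitivity troponin I or T (whichever is used in each center"), but the document does not show that it exists.

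The continuity correction has a similar effect for an unrelated reason: it lowers the test statistic whether or not centres differ.

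What is at stake is efficiency. In a borderline result the centre-adjusted analysis could reach significance while the planned test does not, and as a sensitivity analysis it could not carry the primary claim.

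**Working it through.** **1. Inputs.** From the article: 25% and 17%, 572 per arm, about 16 centres, 1:1 allocation within centre, final level 0.049. Assumed, because the document gives no value: between-centre SD of the log-odds (τ) of 0, 0.25, 0.5 or 0.75. At a mean risk of 25%, the last three put 90% of centres between 17.9% and 33.1%, 12.1% and 41.7%, and 7.9% and 50.2%.

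**2. The plan's own figure.** Without correction,
n = [1.960·√(2·0.21·0.79) + 1.2816·√(0.25·0.75 + 0.17·0.83)]² / 0.08² = 542.7 per arm.
With correction,
(n/4)·[1 + √(1 + 4/(n·0.08))]² = 567.4, so 568 per arm, or 1136 in total. At level 0.049 the total is 1142. The stated 1144 is reproduced only with the correction (without it, 1086 to 1092). Group-sequential power at 572 per arm is 90.1%. The stated boundaries also reproduce.

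**3. Effect of the correction alone.** It subtracts 1/572 = 0.00175 from the absolute difference. Under the null at 25% the standard error is √(0.25·0.75·2/572) = 0.0256, so the statistic falls by 0.068. Size at nominal 0.05 is 2·[1 − Φ(1.960 + 0.068)] = 0.043. At 0.049 it is 2·[1 − Φ(1.969 + 0.068)] = 0.042, and simulation gives 0.040. Power at 572 per arm and level 0.05 is 91.4% without the correction and 90.2% with it, a cost of 1.2 points.

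**4. Effect of ignoring centre alone.** With balance within centres, the true variance is the assumed one times 1 − Var(p_k)/[p(1 − p)], where p_k is the risk in centre k. This is roughly 1 − τ²·p(1 − p). For τ = 0.5 and p = 0.25 it is 1 − 0.25·0.1875 = 0.953, so the true standard error is 0.976 of the one used. Size without correction is then 2·[1 − Φ(1.960/0.976)] = 0.045. Simulation gives the same.

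**5. Both together, by simulation** (1144 patients, 16 equal centres, level 0.05, 100,000 runs per cell):

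| τ | Size: planned | Size: unadjusted, no correction | Size: CMH, no correction | Power: planned | Power: CMH, same correction | Power: CMH, no correction |
|---|---|---|---|---|---|---|
| 0 | 0.043 | 0.050 | 0.050 | 90.4% | 90.3% | 91.5% |
| 0.25 | 0.042 | 0.049 | 0.050 | 90.3% | 90.4% | 91.6% |
| 0.5 | 0.038 | 0.045 | 0.050 | 90.6% | 91.2% | 92.4% |
| 0.75 | 0.034 | 0.040 | 0.050 | 91.0% | 92.2% | 93.2% |

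Planned test against CMH with the same correction isolates centre: about 0, 0.1, 0.6 and 1.2 points. CMH with against CMH without the correction isolates the correction: 1.1 to 1.2 points.

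**6. At the final level of 0.049**, for the same four values of τ, the planned test has size 0.040, 0.040, 0.036 and 0.034 and power 90.2, 90.1, 90.8 and 90.9%. CMH without correction has size about 0.048 and power 91.5, 91.4, 92.4 and 93.2%. A run with unequal centres at τ = 0.5 agrees: 90.3% against 92.1%.

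**7. Baseline covariates.** With no centre differences and an ignored covariate of log-odds SD 0.5 or 1.0, the uncorrected test has size 0.050 and 0.049, so type I error is unaffected. With τ = 0.5, a logistic model with centre and that covariate has power 92.8% (covariate SD 0.5) or 95.4% (SD 1.0), against 90.4% and 90.6% for the planned test. The gap of about 2 to 5 points also contains the centre and correction shares from step 5. It is slightly flattering too, because the Wald test in that model ran a little above nominal size (0.052 to 0.054).

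**The case against.** The best defence is that nothing promised is missed. The trial was sized on this very test, the 1144 reproduces, power stays at or above 90% for every assumed τ, and type I error is controlled. The test needs no model, compares the same two proportions as the sample-size section, and is backed by a prespecified mixed model with centre. All of this stands. The planned test has real merits, and the question is only which valid analysis should be primary.

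Four stronger readings are tempting, and the document supports none of them.

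- **The confirmatory p-value is wrong or the trial underpowered.** A conservative test is valid, and the power target is met.
- **Omitting baseline variables makes the test conservative.** It does not. Only the stratification factor and the continuity correction do that.
- **The whole gain from switching to CMH is due to centre.** At τ of 0 or 0.25 nearly all of it comes from dropping the correction.
- **Covariate adjustment would bring power to about 95%.** That needs a prognostic strength the article does not give. Under the weaker assumption the figure is 92.8%.

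Nor does the local choice of troponin assay prove that event rates differ by centre.

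Deferral to a later analysis plan is not a full answer, because the article itself names the primary test and places the centre-adjusted model among the sensitivity analyses.

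**Conclusion.** The point holds as a modest, free improvement. The planned test is valid and has its stated 90% power, but its size at nominal 0.049 is about 0.040 from the correction alone, and about 0.036 to 0.034 if centres differ with τ of 0.5 to 0.75. Ignoring centre costs about 0 to 1.2 points of power and the correction about 1.2, so roughly 1.2 to 2.3 points together at 1144 patients.

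The centre share rests on an assumed τ, normal centre effects on the log-odds scale and near-complete balance within centres. If centres hardly differ, it vanishes. The correction share does not depend on τ. Any further gain from covariates cannot be sized from the document.

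**What to change.** Before the unblinded interim analysis, amend the protocol and write into the analysis plan that:

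- the primary analysis, at both the interim and the final look, is a CMH test stratified by centre, without continuity correction, at the boundaries already stated;
- the effect is reported as a centre-stratified risk difference with its confidence interval;
- very small centres are pooled by a rule fixed in advance, which matters most at the interim, when centres are smallest;
- the unadjusted test becomes a sensitivity analysis.

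Adjustment for a short prespecified list of baseline variables is optional. If it is wanted, check the size of the chosen method with 16 centre terms first, given the slight excess seen with the Wald logistic test.

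The cost is wording only. No extra patients or data are needed, and the sample size of 1144 can stand, since the new test has at least the planned power.

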#### Methods against bias

Screening logs will be collected to assess the risk for selection bias in patient recruitment. Randomization codes will be provided by an independent biostatistician to ensure blinding as long as practical. Participating patients, outcome adjudicators, and data analysts will be blinded to group assignment. Furthermore, a blinded outcome committee will be implemented to avoid detection bias. Anesthesiologists treating patients assigned to personalized management cannot be blinded as the results of preoperative automated blood pressure monitoring are necessary for perioperative personalized blood pressure management.

### Data management and monitoring

Patient data will be documented by dedicated trial personnel and managed in an eCRF using a trial management software. Data will be entered via an encrypted connection (HTTPS) in web browser input masks. Each patient will be given an identification number to ensure pseudonymized data analysis. Each change in the data, e.g., due to resolved queries, will be documented by an automated audit trail. Pseudonymized data will be stored in accordance with local data protection laws.

Trial site monitoring will be conducted to ensure that the rights and well-being of patients are protected; that the reported trial data are accurate, complete, and verifiable; and that the conduct of the trial follows the currently approved protocol/amendment(s), with good clinical practice and with applicable regulatory requirements. The monitoring comprises the following tasks: training of the trial personnel prior to trial start (site initiation visit), regular on-site monitoring visits, and a close-out visit at the end of the trial. Central elements of the monitoring are the verification of consent and inclusion criteria, along with trial conduct.

### Data Safety Monitoring Board

Three independent experts—including a biostatistician—will be the members of the Data Safety Monitoring Board (DSMB). DSMB members will meet before trial initiation, 3 months after the inclusion of the first patient, thereafter every 6 months, and after the interim analysis—and more often as they deem necessary or advisable. DSMB members will consider by-group results on a blinded basis. If DSMB members identify safety issues, they will have the prerogative to request unblinded outcomes. DSMB members will advise whether to continue, modify, or stop the trial. DSMB members will act independently from the sponsor and competing interests.

### Dissemination plans

The results of this trial will be published in an international peer-reviewed medical journal. Both positive and negative results will be reported. The principal investigator is responsible for the preparation of the final report and therefore will have access to all available data. The full protocol, anonymized data, and the statistical code used for the analysis will be available from the corresponding author upon reasonable request. Authorships will be based on the recommendations of the International Committee of Medical Journal Editors (http://www.icmje.org/).

## Discussion

In this trial, we will test whether personalized perioperative blood pressure management—based on preoperative automated blood pressure monitoring—reduces the incidence of a composite outcome of acute kidney injury, acute myocardial injury, non-fatal cardiac arrest, and death within 7 days after surgery compared to routine blood pressure management in high-risk patients having major abdominal surgery.

At some level, intraoperative hypotension surely causes organ injury—but the harm threshold for individual patients remains unclear. Perioperative blood pressure targets are thus a matter of current research. In a single-center trial including 451 high-risk patients having major non-cardiac surgery, universally targeting mean arterial pressure ≥ 75 mmHg—compared to ≥ 60 mmHg—did not reduce postoperative major adverse cardiovascular events [12]. Interestingly, the authors of this trial conclude that we should move away from population-based to individualized definitions of hypotension, “which could open the door to a paradigm of personalized intraoperative blood pressure targets” [12]. Using a population harm threshold of 65 mmHg or universally targeting higher pressures for all patients indeed ignores the fact that normal blood pressure varies considerably among individuals [15]. From a physiologic perspective, it is thus reasonable to assume that optimal intraoperative blood pressure depends on each individual patient’s normal blood pressure physiology.

There is only one randomized trial on individualized blood pressure management [13]. The INPRESS trial tested the hypothesis that targeting individual preoperative resting blood pressures reduces the incidence of postoperative systemic inflammation and organ dysfunction within 1 week after surgery compared to routine blood pressure management in 292 high-risk patients having major surgery [13]. Individualized blood pressure management reduced the risk of postoperative systemic inflammation and organ dysfunction compared to routine blood pressure management [13]. However, this small trial had limitations that limit its internal validity. First, this trial not only compared two different blood pressure management strategies but also used two different vasopressors (norepinephrine vs. ephedrine) in study and control group patients. Second, the individual intraoperative blood pressure target was defined based on a single preoperative blood pressure measurement taken in the preoperative evaluation clinic or on the surgical ward the day before surgery. However, single preoperative blood pressure measurements do not adequately reflect individual blood pressure profiles [14–16]. We, therefore, will perform preoperative automated blood pressure monitoring for one night to define individual intraoperative blood pressure targets.

Automated blood pressure monitoring is the clinical reference method to assess blood pressure profiles [29] and an international consensus group recently defined it as “the optimal method to establish baseline values” before surgery [17]. We will define nighttime as 00:00 to 06:00 h [20, 21] and thus exclude retiring and rising periods (evening 21:00 to 00:00 h; morning 06:00 to 09:00 h) which are subject to considerable variation [20, 21].

We will include high-risk patients having major abdominal surgery to ensure that the studied population is broad and representative of the patient population benefiting from hypotension avoidance [30]. Participating trial centers will be mainly large university medical centers with many high-risk patients having different types of major abdominal surgery procedures.

Our chosen outcomes are clinically relevant and are recommended by an expert consensus panel of the StEP initiative [31, 32]. Standardized and precisely defined outcomes ensure valid comparisons between different trials [33]. The primary composite outcome includes major perfusion-related complications within 7 days after surgery. Considering complications within the first 7 postoperative days minimizes the risk of complications being confounded by postoperative events rather than intraoperative blood pressure management. In addition, most patients are still hospitalized during the first 7 postoperative days, which allows a more accurate outcome assessment. We will also assess the incidence of a composite outcome of need for renal replacement therapy, myocardial infarction, non-fatal cardiac arrest, and death within 30 and 90 days after surgery.

In summary, we will perform a randomized trial to test the hypothesis that personalized perioperative blood pressure management—based on preoperative automated blood pressure monitoring—reduces the incidence of a composite outcome of acute kidney injury, acute myocardial injury, non-fatal cardiac arrest, and death within 7 days after surgery compared to routine blood pressure management in high-risk patients having major abdominal surgery.

